### **2.3.3 Study design**

A prospective cohort study design will be used to follow up players for a period of two consecutive seasons.

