### **2.3.2 Objectives**

- a. To determine the difference in etiology, nature, severity and location of injuries between first and second division soccer players
- b. To assess whether there is any relationship between injury pattern and players' age, playing position and division of play.
- c. To assess if there is any difference in injury pattern according to training and match exposure
- d. To describe the availability of the medical support into the teams

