teams and players at the end of the season 2014-2015 which allows teams to reorganize and recruit new players. Changes that will take place during this period will be noted and appropriate actions will be done to allow the injury surveillance to continue in the subsequent season. The study two with intervention will commence at the beginning of the season 2015-2016.

Figure 2: Study one framework

[figure not shown]

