### **2.3.9 Statistical analysis**

All data will be analyzed statistically using STATISTICA version 12. Standard descriptive statistics will be used for numerical variables as means, standard deviations (SD) or 95% confidence intervals (CI).

In this study incidence for all injuries will be expressed as injuries per 1000 soccer playing hours for the purpose of the comparison with previous epidemiological studies. Risk per 1000 hours of exposure either per match, training or both will be equal to number of injuries multiplied by 1000 per total exposure time. The variations of injuries during match, training or both for the two seasons will be analyzed using Analysis of Variance (ANOVA). ANOVA will also be used to analyze the occurrence of injuries according to the position in the team and division of play. The categorical variables such as the frequency, type, location, severity as well as the mechanism of injuries will be analyzed using a Chi-square test or Fisher's exact test for small numbers. Between groups incidence of injuries will be compared using z-statistics and rate ratios (RR) with a 95% CI will used to present data. The level of significance for all the tests is set to 0.05. Univariate and multivariate regression analyses will be used to calculate odds ratios (ORs) and 95% confidence intervals (CIs) for  $\pm 1$  standard deviation of change. The details of all the statistical analysis that will be performed are provided in the appendix J.

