Coaches will also be trained on first aid. During the training, they will receive the first aid course for two days that will be provided by the trainer from the Rwanda Red Cross. Questionnaires will be distributed to the coaches to assess their knowledge immediately after first aid training. At the end of season two (June 2016) questionnaires will be distributed to the coaches from both divisions to assess the knowledge retained after one year of intervention.

Coaches and medical personnel from the first division will be requested to continue the recording of injuries and exposure using the procedure they used in the season one (2014-2015). To increase compliance and proper recording, coaches will be visited at team practice by the researcher to see if proper implementation is occurring and additional instructions on the correct conduct of the exercises will be provided where necessary. Data collection during season two (2015-2016) will be the same as season one where players exposure time, occurrence of injuries, treatment will be assessed.

Figure 3: Study two framework

[figure not shown]

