#### **2.4.8 Statistical analysis**

Analysis of the incidence of injuries comparing the two study groups and the two divisions will be done as explained in the study one. Demographic characteristics of the coaches and responses on the knowledge, perception, readiness and decision making assessment will be analysed using descriptive statistics (range, mean, standard deviation). Categorical data like the coaches’ level of education, highest level of coaching license, availability of the medical personnel into the team will be presented as frequency and percentages. The five injury prevention readiness to practice questions will be coded from zero to five. The minimum score will be zero and the maximum score will be 25. The responses from the perception questions that are on a 5-point Likert scale will be recorded on a range from 1=“very unlikely” to 5=“very likely”. Therefore the results will be analysed using the descriptive statistics with means and standard deviation. Pearson correlation will be used to assess the relationship between perception variable and coaches’ readiness of sports injury prevention. The same test will be used to assess the association between readiness, perception, and first aid knowledge and compliance with the injury prevention programme. Analysis of variance test (ANOVA) will be used to analyse the difference between the coaches’ perceptions, knowledge, and readiness regarding injury prevention in the first division and the second division. The level of significance for all the tests

is set to 0.05. The details of all the statistical analysis that will be performed are provided in the appendix J.

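### Study One's season and division comparisons use 2015-16 data, when about half the second-division teams are on the trial intervention, and the visible plan does not separate those teams

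*Combined protocol and SAP*

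**What the plan says.** Section 2.3.3 sets the follow-up of Study One: "A prospective cohort study design will be used to follow up players for a period of two consecutive seasons". Section 2.3.6.1 places the first season in 2014-15 and says of the next that "appropriate actions will be done to allow the injury surveillance to continue in the subsequent season". The same section adds: "The study two with intervention will commence at the beginning of the season 2015-2016". Section 2.4.7.1 confirms that one recording system serves both studies: "Data collection during season two (2015-2016) will be the same as season one".

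The trial is confined to the second division (section 2.2), and its 19 teams are split into groups of nine and ten (section 2.4.4.4).

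Section 2.3.9 analyses this material by season, "The variations of injuries during match, training or both for the two seasons will be analyzed using Analysis of Variance (ANOVA", and by division: "ANOVA will also be used to analyze the occurrence of injuries according to the position in the team and division of play". A contrast between divisions is also the first objective in section 2.3.2. Section 2.4.8 then says that the incidence analysis "comparing the two study groups and the two divisions will be done as explained in the study one". Neither analysis section limits a comparison to season one, sets the intervention teams aside in season two, or includes a term for the intervention. Both refer to Appendix J for details.

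**The concern.** Study One is meant to describe injury risk under usual conditions. In its second season, roughly half of one division is receiving a programme intended to lower that risk, and the other division is not. Intervention status is therefore tied both to season (it exists only in 2015-16) and to division (it exists only in the second).

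A season comparison that does not separate these teams cannot tell a change in background risk from an effect of the programme. A division comparison that draws on season two has the same difficulty. Position and risk-factor analyses that use season two would describe a mixture of treated and untreated players. If the programme works, the surveillance figures would understate usual risk in the second division, and part of a reported season or division difference would be the trial intervention under another name.

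**Working it through.** The plan gives no figure for this overlap, so there is none to reproduce. The check asks how far the comparisons would move.

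**Inputs**
- Teams: 14 first division, 19 second division (section 2.3.4).
- Intervention teams in season two: k = 9 or 10 of 19 (section 2.4.4.4); none in the first division (section 2.2).
- Programme effect: RR 0.65, an injury-risk result cited in section 1.1; RR 0.80, the 20% reduction in section 2.4.4.3 read as relative; RR 1.0, because section 1.1 also cites studies with no significant effect. If the 20% is read as absolute (70% to 50%), the ratio is 0.50/0.70 = 0.714, between the first two.
- Assumptions: equal exposure per second-division team and in each season; no other season change; control teams unaffected.

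**Share treated**
- Second division, season two: 9/19 = 47% to 10/19 = 53%.
- Second division, both seasons: 9/38 = 24% to 10/38 = 26%.
- All team-seasons: 33 × 2 = 66; 9/66 = 13.6% to 10/66 = 15.2%.

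**Second-division rate relative to its untreated value**
- Season two: F = 1 − (k/19)(1 − RR).
- Both seasons combined: (1 + F)/2.
- Multiplier on the first-to-second rate ratio: the reciprocal of each.

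| RR | k | F, season two | Multiplier, season two | (1 + F)/2 | Multiplier, both seasons |
|---|---|---|---|---|---|
| 0.65 | 9 | 0.834 | 1.20 | 0.917 | 1.09 |
| 0.65 | 10 | 0.816 | 1.23 | 0.908 | 1.10 |
| 0.80 | 9 | 0.905 | 1.10 | 0.953 | 1.05 |
| 0.80 | 10 | 0.895 | 1.12 | 0.947 | 1.06 |
| 1.00 | 9 or 10 | 1.000 | 1.00 | 1.000 | 1.00 |

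F is also the apparent season-two to season-one ratio in the second division when background risk does not change. Adding first-division teams to the season comparison would dilute this apparent change but not remove it.

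**After a restriction.** Season one alone contains 33 team-seasons, none treated. Keeping season two without the intervention teams leaves 66 − 9 = 57 or 66 − 10 = 56 team-seasons, again with none allocated to the intervention.

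**The case against.** Several points on the other side have force.

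- **Pooling is not stated.** A reader might infer that the plan merges the two seasons to compare divisions. The text does not say so; it only sets no season limit. The both-seasons column is therefore conditional. The season comparison in section 2.3.9 needs no such inference, because it must use season-two data.
- **Appendix J and Figure 2 cannot be read here.** A restriction may stand there. If so, sections 2.3.9 and 2.4.8 should state it.
- **Change over time is partly intended.** Section 2.4.2.1 lists a before-and-after objective and a comparison between groups or over time, and first-division recording in season two could serve as an untreated reference. This is a reason to keep these comparisons but separate the arms within them.
- **Direction.** It is tempting to say that a first-division excess would be exaggerated. No passage says that the first division has the higher rate, and section 2.4.4 describes second-division coaches as less supported. If the second division's rate is higher, the same bias would hide a difference.
- **Effect size.** The bias exists only if the programme changes injury risk, and section 1.1 reports mixed results.
- **Scope of the figures.** They concern overall injury rates. The section 2.3.2 objective, "To determine the difference in etiology, nature, severity and location of injuries between first and second division soccer players", concerns the pattern of injuries, which the table does not measure.
- **Repeated players.** One might read the season ANOVA as treating the same players in two seasons as independent groups. Section 2.3.9 does not specify the form of the ANOVA, so that criticism is not supported.

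**Conclusion.** The point holds. Followed as written in the visible sections, the season comparison includes 9 or 10 treated team-seasons, as does any division, position or risk-factor analysis that uses 2015-16 data, and nothing identifies or removes them.

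If the programme works, the second-division rate is biased downward relative to the first division. The first-to-second ratio is multiplied by between 1.10 and 1.23 in season two over the effects RR 0.80 to 0.65, and by between 1.05 and 1.10 if both seasons are combined. With no effect there is no bias. These sizes rest on equal exposure per second-division team and season, and on control teams being unaffected.

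A reader should not conclude that the trial itself is compromised. The randomised comparison between arms is untouched, as is every estimate from season one alone. The defect is in Study One's use of season two and in the division comparison of section 2.4.8, and should be corrected there. The conclusion is subject to what Appendix J contains.

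**What to change.** 1. **Section 2.3.9, division, position and risk-factor analyses.** Use season one plus season-two data from teams not allocated to the intervention, or keep all team-seasons and add an indicator for the intervention being in use. If teams are left out, include season in the division model: 19 of the remaining 28 or 29 second-division team-seasons would come from season one, against 14 of 28 in the first division.
2. **Section 2.3.9, season comparison.** Report the change from 2014-15 to 2015-16 separately for first-division, control and intervention teams. This keeps the before-and-after objective of section 2.4.2.1.
3. **Section 2.4.8.** Restrict the season-two division comparison to non-intervention teams or stratify it by arm. It need not be deleted.
4. **Define untreated.** Section 2.2 gives control-group coaches additional training in first aid, treatment and rehabilitation. Section 2.4.6 places first aid training in the intervention, and section 2.4.9 says that control teams keep their usual warm-up. These passages must be reconciled before control teams can be labelled untreated.

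The cost is a short revision of two analysis sections and one clarification; no new data are needed. Between 9 and 10 of 66 team-seasons (14-15%) are dropped or flagged, with slightly less precision in Study One.

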### **2.3.4 Participants**

The Federation of Rwandese Football Association (FERWAFA) organizes tournaments at different levels. The top flight male first division is composed of 14 teams while 19 clubs compete in the second division.

The first division competition is the country's primary soccer competition. There are 14 men's association soccer clubs that participate in the league and it operate on the process of promotion and relegation. The teams play 26 matches, where each club plays the others twice, during the season which runs from September to June. The total number of matches is 364 matches. The league is currently sponsored by the largest brewer and soft beverage company in Rwanda on its band new beer named "turbo king" and thus officially known as "turbo king national football league". At the end of the completion, the teams are ranked according to the total points accumulated during the season. In case of equal number of points the goal calculation of the number of goals scored and conceded come in favor of the team to determine the winner. The

league winner qualifies to represent the country in the CAF champions' league while the two lowest placed teams are relegated into the second division. Many teams in the first division are sponsored either by private business companies or government institutions (for example, the police, the army and other governmental parastatals) (FERWAFA, 2008).

There are 19 teams competing in the second division organized by the FERWAFA. Unlike the first division, the second division teams do not play each other because each team would play 36 games. Playing many games require many resources from the teams, the organizing federation as well as a longer period of time. Therefore the teams are randomly divided into two groups. Group A composed of 10 teams and group B composed of 9 teams. Teams in each group play each other and accumulate the points according to the win or draw rules. The first two teams in each group qualify to the semifinal stage where they play the teams from the other group. The winners of the semifinal stage qualify to the final and are automatically promoted to the first division. The competition ends while the teams play between 11 and 12 matches. The second division season runs from November to May. The FERWAFA requires each team to register maximum 30 players; therefore the maximum number of players that will participate in this study are 990.

### **Inclusion criteria**

Players who will be having contracts with the teams will be included in this study. Prior to the start of the league players undergo a medical assessment to be cleared and issued a playing license. Therefore, players having a valid license to participate in the league from the FERWAFA will be included. Players presenting injury at the beginning of the study will be included when cleared to join teams' training and matches. Data from players who will be selected to participate in the national team will also be included in the study.

### **Exclusion criteria**

Players who will not agree to participate in the study will be excluded from the study.

## **2.3.5 Data collection instruments**

### **2.3.5.1 List of the players**

The list of all the players will be obtained from the FERWAFA (Appendix A). It will be sent to the teams while additional information pertaining to age, playing position, number of years playing soccer and number of year in the current team will be needed.

### **2.3.5.2 Medical record form**

Additionally, the medical record form in terms of questionnaire (Appendix B) will also be sent to the players to screen information pertaining to the past medical history of the players. The history of injury would be assessed including the number of injuries sustained, causes, mechanisms, body part affected, type as well as the treatment received.

### **2.3.5.3 Exposure form**

A specific player exposure form developed by FIFA will be used to record detailed information regarding player involvement in soccer (Fuller et al., 2006) (Appendix C). The forms will be given to the coaches to record duration of the training sessions. Match exposure will be gathered from the referees' reports submitted to FERWAFA. Any form of physical activities supervised by the coach that the players will undertake during training will be recorded as training exposure time. Match exposure time is defined as the amount of time the player will be involved while the team is playing against another team. The duration of the training will be recorded from the start of the warm up to the end of the cool down session (Parry & Drust, 2006). Exposure form will also record player absence from training and competition and the reason for this absence. The forms will be collected by the research team once in two weeks.

### **2.3.5.4 Injury registration form**

Similar to the exposure form, an injury report form (Appendix D) will be used to collect data pertaining to the incidence of injuries by the team medical personnel or the research assistant for

the teams that do not have any medical personnel (Fuller et al., 2006). The form is comprehensive and designed in such a way that the injuries are recorded on the front side of the page while all the definitions pertaining to the type, anatomical location, severity and circumstance of injury are provided at the back page of the form. The form has been developed and used during major FIFA tournaments and Olympic games (Junge, 2004) and has been extensively used in other studies (Junge et al., 2011) but is not routinely used in soccer in Rwanda. For example an injury is defined as any physical complaint that resulted from soccer participation whether in training or match. It does not necessarily mean that there is a need or not of medical attention.

A meeting with the team medical personnel will be organized to explain to them about the purpose of the study and their role in the study. They will be given the report forms to record any injury that will happen during the time of the study. Further explanations will be given to them as to specific definitions and the way of recording.

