##### **Objectives**

- a. To determine the difference in etiology, nature, severity and location of injuries between first and second division soccer players
- b. To assess whether there is any relationship between injury pattern and players' age, playing position and division of play.
- c. To determine whether nonmodifiable and modifiable intrinsic risk factors predict the risk of sustaining an injury in male soccer players in Rwanda.
- d. To assess if there is any difference in injury pattern according to training and match exposure
- e. To determine whether the availability of the medical support into the teams is associated with the incidence of re-injuries

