#### **2.4.4 Participants**

Coaches and assistant coaches of the teams in the second division teams will participate in this study. The coaches have been the center of focus in recent years as the main actors in the development of soccer in Rwanda. Much training has been organized by FIFA and CAF to enhance the knowledge and practice of the coaches. Trainings pertaining to technical, tactical and physical performance of the players were provided. At the end of the training, coaches are provided certificates. Not all coaches in Rwanda are citizens and not all of them had the same training. There are therefore some differences that may arise from their coaching training, background and experience.

The coaches are required to plan and supervise training sessions to develop the fitness and the skills of the payers. Coaches are responsible for the development of the training sessions according to the demands of the competition and the period of the season. The involvement of the coach in the first division teams concerning injuries in Rwanda is relatively less compared to the coaches in the second division because the teams have medical personnel who provide assistance. They also have assistant coaches, sometimes goalkeeper coaches, and kit managers. Coaches in the second division do not have all the support needed for their work. Working with

young players, they are required to act as organizers, parents, teachers, counselors, discipliners, for them to achieve results. In the case of injuries, coaches are looked at as mature and responsible people to provide first aid, preliminary management and advice for treatment. Coaches are further responsible to allow the players to return to play after injuries.

There are 19 teams in the second division and each team has at least one head coach. The minimum number of coaches of the teams who will receive the training is 19. The assistant coaches and goalkeeper coaches of the teams in the intervention study will also participate in the study even though not all the teams have them. The total number of players participating in the in the second division league is 570.

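### The injury recorder changes with medical support, so the re-injury objective cannot separate support from recording, and the division incidence comparisons are exposed to an unstated degree

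*Combined protocol and SAP*

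**What the plan says.** **Recorder.** Under 2.3.5.4 the injury form "will be used to collect data pertaining to the incidence of injuries by the team medical personnel or the research assistant for" any team lacking such staff. The event is broad: every physical complaint arising from playing or training counts, whether or not it needs medical attention.

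**Objectives.** Section 1.3 lists, for Study One, objective a, "To determine the difference in etiology, nature, severity and location of injuries between first and second division soccer players", and objective e, "To determine whether the availability of the medical support into the teams is associated with the incidence of re-injuries". The list in 2.3.2 repeats objective a but has no item e. Its only item on medical support is descriptive: "To describe the availability of the medical support into the teams".

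**Where the staff are.** Section 2.4.4 says that the first-division coach's involvement with injuries "is relatively less compared to the coaches in the second division because the teams have medical personnel who provide assistance". It describes second-division coaches as lacking part of the support they need, and as giving first aid and deciding on return to play. It does not say how many second-division teams have medical staff. Under 2.4.7.1, first-division medical personnel go on recording in season two.

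**Analysis.** Section 2.3.9 analyses injury occurrence by division with ANOVA, compares incidence between groups with z-statistics and rate ratios, and treats type, location, severity and mechanism as categorical variables. It describes no term for recorder and no check on completeness of capture. Section 2.4.8 carries the division comparison of incidence into Study Two.

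**A second source.** Section 2.3.5.3 adds: "Exposure form will also record player absence from training and competition and the reason for this absence". Coaches receive this form in every team (2.3.6.1).

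**The concern.** A comparison of incidence is fair only if events are found equally well on both sides. Here the person who finds and writes down the injury is determined by the factor that objective e studies. The broad definition makes this matter more, because whether a minor complaint is counted depends on who is present and asking.

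The bias could go either way. Staff who are with the team daily may hear of more minor complaints, while a research physiotherapist may ask more actively. More players or a second season would narrow the confidence interval around a biased value without moving it.

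At stake is whether a difference in re-injury between teams with and without medical support, or in incidence between divisions, can be read as a difference in risk.

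**Working it through.** **1. Inputs.** There are 14 first-division and 19 second-division teams, with at most 30 players each (2.3.4). The plan's maximum of 990 reproduces: (14 + 19) × 30 = 420 + 570 = 990. That figure is not in dispute. Let *m* be the number of second-division teams with medical staff; the plan does not give it. From 2.4.4, all 14 first-division teams are taken to have staff.

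**2. Objective e.** For each team, support = 1 if it has staff, and recorder = 1 if staff do the recording. By 2.3.5.4 these are equal in every team. A model with an intercept, support and recorder has three columns but rank 2 for *m* = 0 to 18. At *m* = 19 no team lacks staff, so there is no contrast at all. No value of *m* and no adjustment separates the two effects.

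**3. Division.** The squared correlation between division and recorder is 14(19 − *m*) / [19(14 + *m*)], and the variance inflation factor (VIF) is 1/(1 − that value).

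| *m* | squared correlation | correlation | VIF |
|---|---|---|---|
| 0 | 1 | 1 | infinite |
| 2 | 238/304 = 0.783 | 0.89 | 4.6 |
| 5 | 196/361 = 0.543 | 0.74 | 2.2 |
| 10 | 126/456 = 0.276 | 0.53 | 1.4 |

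The tie is complete only at *m* = 0. For *m* between 1 and 18 a recorder term could in principle be fitted, but none is described. At *m* = 19 every team has the same type of recorder and the tie disappears.

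**4. Size for incidence.** With equal true rates, observed rate ratio = capture by staff / capture by assistants. The documents give no capture figures, so these are assumptions: 0.90/0.70 = 1.29; 0.70/0.90 = 0.78; 0.90/0.80 = 1.13. For the division contrast, second-division capture is [*m* × staff + (19 − *m*) × assistants]/19. With staff 0.70 and assistants 0.90:

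- *m* = 0: 0.70/0.90 = 0.78
- *m* = 5: (3.5 + 12.6)/19 = 0.847, ratio 0.83
- *m* = 10: (7.0 + 8.1)/19 = 0.795, ratio 0.88

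**5. Chance of a false finding, for scale only.** Section 2.4.4.3 cites about 70% of players injured. Taking one injury for each such player gives 0.70 × 420 = 294 and 0.70 × 570 = 399 true injuries. Exposure per player is taken as equal, clustering is ignored, and the 0.05 test is taken as two-sided.

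For staff 0.70, assistants 0.90 and *m* = 0, the recorded counts are 205.8 and 359.1. The standard error of the log ratio is √(1/205.8 + 1/359.1) = 0.087, and |ln 0.778|/0.087 = 2.87. The chance of p < 0.05 is about 82%, falling to 29% at *m* = 10. For staff 0.90 and assistants 0.80 it is 29% at *m* = 0 and 10% at *m* = 10.

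**6. Re-injury.** The glossary requires the same type and site after return to full participation, so both the index and the repeat injury must be recorded. If each were captured independently with the fractions above, the ratio for re-injuries per hour would be the square: 1.29² ≈ 1.65, or 0.78² ≈ 0.60. Independence is a further assumption.

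**7. Objective a.** If a recorder captures every kind of injury with the same fraction *c*, the recorded share of kind *k* is *c*·n_k / (*c*·Σn) = n_k/Σn, and *c* cancels. The profile is distorted only if *c* differs by kind, for example if one type of recorder misses more slight injuries. The ratios in steps 4 to 6 do not measure that.

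**The case against.** The plan does take steps to standardise recording. All recorders use one form with definitions on the back; medical staff are briefed on definitions and recording (2.3.5.4, 2.3.6.1); assistants are physiotherapists trained on the FIFA and UEFA guidelines. These should narrow any gap in capture. They do not make recorder and support separable, and preparation is unequal: assistants train in the field with a youth team, while staff attend a meeting.

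Objective e may not be live, since 2.3.2 replaces it with a descriptive item. That stands, and it makes reconciling the lists the first step. Appendix J, to which 2.3.9 defers for detail, is not in the text reviewed, so a recorder adjustment there cannot be excluded. It could help the division comparisons, but not objective e.

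A reader might infer four stronger conclusions that the documents do not support:

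- **That division and recorder coincide.** Section 2.4.4 says second-division coaches lack some support, not that their teams have no medical staff. Section 2.4.7.1 allows for new medical personnel arriving in teams, and the coaches' questionnaire treats availability as something that varies by team.
- **That objective a fails in the same way.** It concerns the profile of injuries, from which uniform under-capture cancels.
- **That the rate ratios above estimate the bias.** They rest on assumed capture.
- **That time-loss data would remove the problem.** Type and site still come from the injury form. Absence may itself vary with support, because the glossary ties the end of an injury to clearance by medical staff while 2.4.4 leaves return to play in the second division to coaches.

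**Conclusion.** The point holds within limits. For objective e as worded in 1.3, recorder and medical support are identical by design, so an observed association cannot be attributed to support rather than to recording. This rests only on the recorder rule in 2.3.5.4. For the occurrence and incidence comparisons by division, the exposure ranges from complete (no second-division team with staff) to none (all 19 with staff), and the plan does not say where in that range it lies. Objective a is affected only through capture that differs by kind of injury.

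Under assumed capture of 90% against 70%, equal true rates would appear as a ratio of 1.29 or 0.78. True size and direction are unknown. The plan should be changed, because the data for a partial check are already being collected. The change reduces the bias and makes it visible without eliminating it.

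**What to change.** 1. **Reconcile the objectives.** Decide whether objective e in 1.3 or the descriptive item d in 2.3.2 is intended, and make the two lists agree.

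2. **Add a common-source analysis.** For the incidence comparisons by division and by medical support, pre-specify a time-loss analysis: at least one training session or match missed with injury as the reason, taken in every team from the coach-completed exposure form. Because match exposure comes from referees' reports, state who enters match absences and their reasons. Present this beside the all-complaint analysis, with recorder type reported for each team. Time loss fits the glossary, whose severity scale starts at one day of absence.

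3. **Check capture.** Compare injury forms with injury absences by one rule in every team, and report agreement by recorder type. Both forms are already collected every two weeks.

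4. **If objective e is retained,** analyse it within division, using the medical availability collected in section B of the coaches' questionnaire (2.4.5.1). Restrict index and repeat injuries to those matched to a recorded absence. This removes confounding with division but not the tie to recorder. Report the number of second-division teams with staff, and state that if there are none the objective cannot be answered.

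5. **State the remaining limits.** Type and site still come from the injury form, and absence and return decisions may vary with support. Report objective e as an association not separable from recording.

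Cost: analysis wording and some linkage work, with no new data form. There will be fewer events, because complaints without absence leave the time-loss analysis, and the within-division contrast may rest on few teams.
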